## Interventions

### Explanation for the choice of comparators {6b}

Optimized SPC charts were identified following systematic evaluation of 13 years of data from 58 DICON hospitals (1.35 million procedures and 14,147 SSIs) [22]. Optimized SPC methods include a logical disjunction of 2 different variations of moving average (MA) charts (i.e., signals are generated whenever either chart features an out-of-control point). Chart A evaluates local SSI rates against medium-term historical SSI rates (18-month reference period with a 6-month lag) for the same procedure type across all other DICON hospitals and aggregates these differences using a 12-month MA. Chart B evaluates current SSI rates against recent SSI rates (3-month baseline interval with a 3-month lag) for the same procedure type at the same hospital and aggregates these differences using a 6-month MA (Fig. 1). Therefore, while the former chart can detect long-term differences between local and DICON SSI rates, the latter is highly sensitive in identifying sustained, short-term local increases in SSI incidence, irrespective of the network-wide DICON rate. Both charts employ a narrow control limit of 1 standard deviation and are thereby tuned for screening potential signals, rather than detecting only definite signals and rejecting those unlikely to represent definitive outbreaks. Correspondingly, this specific chart combination reached sensitivities of 0.9 and 0.88, and specificities of 0.67 and 0.75, on the training (initial 12 years) and validation (last year of data) subsets, respectively. In contrast, traditional SSI surveillance has a reported sensitivity of only 33% to 65% [23, 24].

**Fig. 1 Fig1:**
[figure not shown]
Example SPC charts used for SSI surveillance in the Early 2 RIS Trial; Chart A (top) is a moving average (MA) chart using DICON baseline rates and Chart B (bottom) is a moving average (MA) chart using local hospital rates

Importantly, SPC surveillance should be viewed as an adjunct to traditional surveillance. That is, traditional surveillance will still be performed in both arms to identify and document SSIs as they occur in study hospitals. In the intervention arm, optimized SPC surveillance will be applied to SSI surveillance data after traditional surveillance is performed to rapidly identify if the data entered and new SSI rates are not in line with expected rates (a “signal”).

### Intervention description {11a}

Data entered locally by infection preventionists at DICON hospitals are transmitted to the DICON Surgical Database per routine practices. Data submitted to the DICON Surgical Database will undergo scheduled weekly analysis by optimized SPC methods. If a signal is generated, study personnel in DICON will be notified to adjudicate the signal and determine if further action is required.

### Criteria for discontinuing or modifying allocated interventions {11b}

N/A. Criteria for discontinuing or modifying allocated interventions were not developed.

### Strategies to improve adherence to interventions {11c}

N/A. Subjects and surgeons will be blinded to study arm.

### Relevant concomitant care permitted or prohibited during the trial {11d}

N/A. Individual patient care will not be impacted by this trial.

### Provisions for post-trial care {30}

N/A. Care will be provided by primary teams throughout the study, not research personnel.

### Outcomes {12}

Primary endpoint (domain: healthcare-associated infection):
Specific measurement – SSI rate, calculated as the number of SSIs per 100 proceduresSpecific metric – Differences in the rates of SSI between the intervention compared to traditional surveillance and feedback alone
SSIs will be defined using standard NHSN definitions
i.DICON personnel train local infection preventionists about how to use and interpret SSI definitions. Thus, standard definitions and methods will be used at all study hospitalsCluster-level risk adjustment will be performed using median surgical volume [25] and median NHSN Risk Index (an operation- and patient-specific risk score that predicts SSI) [26, 27] per clusterMethod of aggregation – Mean rates will be summarized for each cluster for each 3-month study “step”

Secondary endpoints:
Several secondary outcomes will be compared between clusters receiving intervention and clusters receiving traditional surveillance and feedback
Stratified analysis of primary outcome – SSI rates stratified by type of SSI (superficial-incisional, deep-incisional, or organ/space).Descriptive outcomes
◦ Description of and difference in number and type of signals◦ Difference in number of investigations of increased rates of SSI◦ Total number and differences in proportion of signals that led to investigations◦ Proportion of SSIs determined to be potentially preventable, based on preventability score◦ Timing of signals

### Participant timeline {13}

All hospitals and clusters will participate for the entire duration of the study, including 1 year of baseline data collection and 3 years of implementation of intervention through a stepped wedge approach. Patients that undergo surgical procedures of interest during the 4-year study period will be followed for up to 90 days post-operatively, per CDC SSI definitions and standard methods.

Randomization will occur at the cluster level within hospitals. Clusters within each hospital will potentially be changed to intervention during 12 “steps” (Fig. 2).

**Fig. 2 Fig2:**
[figure not shown]
Schematic for stepped wedge design for the Early Recognition and Response to Increases in Surgical Site Infection (Early 2RIS) Trial. Gray = control, during which hospitals will receive traditional SSI surveillance, including biannual data reports. Any signals identified in biannual reports or detected by local personnel will undergo further investigation. White = intervention, during which hospital clusters will receive feedback from traditional surveillance and signals generated by applying optimized SPC methods to SSI surveillance data

### Sample size {14}

In our power calculation, we utilized 3 years of pilot data from 101 clusters of procedures in 29 DICON hospitals (including 1622 SSIs following 154,554 procedures). Power was evaluated via a simulation study where for each cluster, log (SSI rate) was generated from a multivariate normal distribution with the following assumptions: (1) cluster-specific SSI rate for traditional surveillance phases calculated from the pilot data (average rate including procedures from all clusters was 1.33%), (2) residual variance for log (SSI rate) of 0.76, (3) within-cluster correlation of 0.36, and (4) between cluster correlation of 0.39 in the same time step and 0.2 in different steps. Based on these assumptions, a study with 101 clusters in 29 DICON hospitals, 12 steps, and an average of 127 procedures per cluster per 3-month step would have 90% power to detect a 25% decrease in the SSI rate between optimized SPC methods and traditional surveillance.

### Recruitment {15}

No specific recruitment will be completed for this study. All participating hospitals are part of DICON.

## Assignment of interventions: allocation

### Sequence generation {16a}

Randomization and allocation sequence will be performed using computer-generated random numbers. However, at most, one cluster per hospital will be changed to the intervention during any individual step; all remaining clusters will continue to receive standard, traditional surveillance and feedback. Once randomized to intervention, clusters will receive surveillance from both optimized SPC and standard methods for the remainder of the study. At the last step, the remaining cluster within each hospital (if any) will begin the intervention.

### Concealment mechanism {16b}

N/A. No concealment was performed.

### Implementation {16c}

The study statistician ([name]) will develop the allocation sequence. The study coordinator ([name]) will assign clusters to interventions as per the randomization scheme.

## Assignment of interventions: blinding

### Who will be blinded {17a}

SSI signals prospectively identified using optimized SPC methods during the intervention period will undergo blinded review to ensure that signal adjudication occurs without knowledge of which hospital cluster generated the signal. Following review, the study coordinator will unblind the signal, and, if the hospital cluster is randomized to intervention, the study team will proceed with the actions required to appropriately respond to the identified increase in SSIs. If the hospital cluster is a control cluster, then the study coordinator will document the signal, but no further action will be taken.

### Procedure for unblinding if needed {17b}

N/A. No unblinding was performed.

## Data collection and management

### Plans for assessment and collection of outcomes {18a}

Routine data on surgical procedures and SSIs will be collected via a standardized limited dataset, per routine DICON practices (Table 2) [28]. No identifiable patient or surgeon data are transmitted to the DICON Surgical Database.

**Table 2 Tab2:** Variables in the DICON Surgical database

All surgical patients	Hospital
	Type of procedure
	Patient identifier
	Date of procedure
	Age
	Sex
	Surgeon identifier
	Start/stop times
	ASA score
	Wound class
	Risk index
	SSI (yes/no)
Patients with Infection	Date of infection
	Type of SSI
	Location at diagnosis
	Organism

When a signal is identified, data will be collected on the rationale for signal adjudication (action vs. no action). If a signal requires action, additional data will be collected for further investigation, per routine protocol.

The majority of data collection will occur through methods already developed and utilized by study hospitals. In brief, each hospital routinely submits limited datasets to the DICON Surgical Surveillance Database, including all variables listed in Table 2. Data definitions and data collection methods are standardized across DICON hospitals. Following signal adjudication, additional data will be collected in a REDCap database to document actions and rationale.

### Plans to promote participant retention and complete follow-up {18b}

N/A. Follow-up will be mandatory and completed through routine SSI surveillance methods.

### Data management {19}

DICON IT personnel will be responsible for data management required for the DICON Surgical Database, per routine DICON practices. The study coordinator will be responsible for documentation required for the study.

REDCap is a toolset and workflow methodology for electronic collection and management of research and clinical trial data. Both REDCap and REDCap Survey systems provide secure, web-based applications that can be used for a variety of types of research, provide an intuitive interface for users to enter data, and have real-time validation rules (with automated data type and range checks) at the time of data entry. These systems offer easy data manipulation and an automated export mechanism to common statistical packages (e.g., SPSS, SAS, Stata, R/S-Plus).

The REDCap program will serve as the portal for data entry by the study coordinator. Data entered into this database will be password protected and only accessible by study personnel. All access to this secure separate database will be monitored and logged.

Surgical data, including SSI data, will be maintained in the DICON Surgical Surveillance Database. Data related to signal adjudication and response will be entered into REDCap databases.

### Confidentiality {27}

This study does not involve the collection of PHI.

### Plans for collection, laboratory evaluation, and storage of biological specimens for genetic or molecular analysis in this trial/future use {33}

N/A. No specimens will be collected for this trial.

## Statistical methods

### Statistical methods for primary and secondary outcomes {20a}

Data will be summarized using standard statistical methods. Analyses will be performed using the intention-to-treat strategy.

#### Primary analyses

The primary outcome will be analyzed using a generalized estimating equations approach with a Poisson or negative binomial model (if overdispersion is detected using Poisson), which will model SSI rate at a cluster level as a function of time (step) and intervention phase (traditional vs. optimized SPC surveillance), while accounting for within-cluster correlation over time and between-cluster correlation within each study hospital. This model will utilize the data from all steps, including the baseline period. To account for any potential residual confounding, we will consider including cluster-level risk-adjustment variables in the model, as described in the previous section. Inference about the model parameter corresponding to the intervention phase will be used to address the main hypothesis (2.1). In case the number of zeroes per cluster exceeds the number of zeroes modeled by Poisson (or negative binomial) distribution, we will consider a zero-inflated Poisson (negative binomial) model.

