**Methods:**

The Early 2RIS Trial is a prospective, multicenter cluster RCT using a stepped wedge design. The trial will be performed in 29 hospitals in the Duke Infection Control Outreach Network (DICON) and 105 clusters over 4 years, from March 2016 through February 2020; year one represents a baseline period; thereafter, 8–9 clusters will be randomized to intervention every 3 months over a 3-year period using a stepped wedge randomization design. All patients who undergo one of 13 targeted procedures at study hospitals will be included in the analysis; these procedures will be included in one of six clusters: cardiac, orthopedic, gastrointestinal, OB-GYN, vascular, and spinal. All clusters will undergo traditional surveillance for SSIs; once randomized to intervention, clusters will also undergo surveillance and feedback using optimized SPC charts. Feedback on surveillance data will be provided to all clusters, regardless of allocation or type of surveillance. The primary endpoint is the difference in rates of SSI between the SPC intervention compared to traditional surveillance and feedback alone.

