### Eligibility criteria {10}

#### Inclusion criteria

All patients who undergo one of 13 targeted procedures at 29 study hospitals will be included in the analysis. These procedures were selected because they are frequently performed in community hospitals and/or are associated with particularly adverse outcomes if complicated by SSI. Eligible procedures will be categorized by type at each hospital using ICD10 codes published by the US CDC’s National Healthcare Safety Network (NHSN) [21]. Clusters will be constructed at each participating hospital based on the type of surgical procedure performed (Table 1). Clusters were constructed to ensure that surgeons who perform similar types of procedures were grouped together to limit potential bias. *These clusters will be the units for randomization and analysis*.

**Table 1 Tab1:** Procedures included in each cluster

Cluster	Procedure
Cardiac	Coronary artery bypass graft
	Cardiac valve replacement
GI	Colon
	Herniorrhaphy
Joint	Knee arthroplasty
	Hip arthroplasty
OB-GYN	Cesarean section
	Hysterectomy
	Vaginal hysterectomy
Spine	Spinal fusion
	Laminectomy
Vascular	Carotid endarterectomy
	Peripheral venous bypass

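### Clusters are defined by procedure type and crossing order is not balanced by type, yet the primary model has no cluster-type term; adding one is cheap and protects precision

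*Protocol article*

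**What the plan says.** The Inclusion criteria section defines the randomized unit: "Clusters will be constructed at each participating hospital based on the type of surgical procedure performed (Table 1". The abstract lists the six types: "these procedures will be included in one of six clusters: cardiac, orthopedic, gastrointestinal, OB-GYN, vascular, and spinal". These clusters are the units of both randomization and analysis.

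On timing, the abstract says "thereafter, 8–9 clusters will be randomized to intervention every 3 months over a 3-year period". Under Sequence generation, "Randomization and allocation sequence will be performed using computer-generated random numbers", with one restriction: "However, at most, one cluster per hospital will be changed to the intervention during any individual step". Any cluster still in control at a hospital crosses at the last step. Nothing spreads the procedure types over the 12 steps.

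The Primary analyses section gives a Poisson or negative binomial GEE "which will model SSI rate at a cluster level as a function of time (step) and intervention phase", "while accounting for within-cluster correlation over time and between-cluster correlation within each study hospital". On covariates, "we will consider including cluster-level risk-adjustment variables in the model, as described in the previous section". The Outcomes section names these as median surgical volume and median NHSN Risk Index per cluster, and presents the adjustment there as planned rather than as something to be considered. Neither section lists cluster type.

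**The concern.** Three features of the protocol treat baseline risk as depending on procedure type:

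- Both control charts compare rates only within the same procedure type (Explanation for the choice of comparators).
- The Risk Index is described as specific to the operation as well as the patient (Outcomes).
- The power simulation uses a separate control rate for each cluster (Sample size).

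The primary model nevertheless has one set of step effects and one phase effect for all six types. In a stepped wedge trial the mix of types among exposed and unexposed clusters changes at every step. With 8–9 clusters crossing at a time, that mix is left to chance. Where the analysis draws on comparisons between clusters at the same step, differences in level between types enter the phase coefficient as noise. What is at stake is precision, from a variable that is known for every cluster before randomization.

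**Working it through.** **Inputs from the protocol.** 105 clusters, 29 hospitals, 12 steps, six types; 127 procedures per cluster-step; target a 25% decrease; power inputs of 101 clusters, variance 0.76 for the log rate, and correlations 0.36 (within cluster), 0.39 (between clusters, same step) and 0.2 (between clusters, different steps). By arithmetic, 105/12 = 8.75 clusters cross per step and 105/29 = 3.6 clusters belong to each hospital.

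**Inputs assumed.** The protocol gives no infection rate or trend by type. Rates by type, their spread and any trend differences below are assumptions. Two-sided alpha of 0.05 is also assumed.

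**Step 1: the plan's own figure.** Power = Φ(|ln 0.75|/SE − 1.96), with |ln 0.75| = 0.288. The SE comes from generalized least squares with step effects, the stated correlations, total variance 0.76 and a Poisson count variance of 1/(127 × rate). The pooled pilot rate is 1622/154,554 = 1.05%; the stated average is 1.33%.

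- 1.05%, four baseline quarters: SE 0.0883, Φ(3.26 − 1.96) = 90.3%.
- 1.05%, 12 steps only: SE 0.0915, 88.2%.
- 1.33%, 12 steps only: SE 0.0859, 91.8%.
- 1.33%, four baseline quarters: SE 0.0830, 93.4%.

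The stated 90% is reproduced under several readings. The implied SE of about 0.083–0.092 sets the scale for what follows.

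**Step 2: chance imbalance alone.** With no sampling noise and assumed rates of 0.8–2.5% by type, the step-and-phase model was fitted over many random allocations. The SD of the spurious log rate ratio was 0.012–0.022 with exchangeable within-cluster correlation and 0.086–0.098 with working independence. The mean was within about 0.01 of zero throughout. The size therefore depends on how far the working structure uses each cluster as its own control.

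**Step 3: effect of adding cluster type, with Poisson counts.** Entries are the SD of the estimated log rate ratio over simulated trials.

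| Assumed rates | Assumed trend difference | Correlation structure | Step + phase | + type | Change |
|---|---|---|---|---|---|
| 0.8–2.0% | none | exchangeable, hospital | 0.100 | 0.077 | −23% |
| 0.8–2.0% | SD 0.1/yr | exchangeable, hospital | 0.103 | 0.075 | −27% |
| 0.8–2.0% (second run) | SD 0.1/yr | exchangeable, hospital | 0.096 | 0.074 | −23% |
| 0.9–2.0% | none | exchangeable, hospital | 0.10 | 0.07 | about −30% |
| 0.9–2.0% | SD 0.1/yr | exchangeable, hospital | 0.108 | 0.084 | −22% |
| 0.8–2.0% | SD 0.1/yr | exchangeable, cluster | 0.064 | 0.062 | −3% |
| 0.9–2.0% | none | exchangeable, cluster | 0.063 | 0.060 | −5% |
| 0.9–2.0% | SD 0.1/yr | exchangeable, cluster | 0.069 | 0.068 | −1% |
| 0.8–2.5% | none | exchangeable, cluster | 0.0698 | 0.0690 | −1% |
| 0.8–2.5% | ±10%/yr | exchangeable, cluster | 0.0659 | 0.0657 | 0% |
| 0.8–2.5% | ±20%/yr | exchangeable, cluster | 0.0707 | 0.0687 | −3% |
| 0.8–2.5% | none | independence | 0.141 | 0.105 | −26% |

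If rates span only 1.0–1.5%, the hospital-grouped gain shrinks to 0.078 against 0.075 (−4%).

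The Monte Carlo SE of an SD is about SD/√(2n). For the 120-trial run (0.103 to 0.075, and 0.064 to 0.062) it is 0.103/√240 = 0.007 under hospital grouping and 0.064/√240 = 0.004 under cluster grouping. The hospital-grouped drop of 0.028 is well outside this. The cluster-grouped drop of 0.002 is within it.

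**Step 4: scale.** Putting that run's SDs into the Step 1 formula gives Φ(0.288/0.103 − 1.96) = 80% without type and Φ(0.288/0.075 − 1.96) = 97% with it under hospital grouping. Under cluster grouping both values exceed 99%. These figures inherit the assumed rates and show relative size only.

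**Step 5: type-by-time.** With cluster grouping, adding type and type-by-time terms changed the SD from 0.070 to 0.069 with no trend difference, from 0.066 to 0.064 at ±10% per year and from 0.071 to 0.064 at ±20% per year. The extra terms help visibly only if trends differ strongly.

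**The case against.** The strongest reply is that the planned model accounts for correlation within clusters over time as well as between clusters in a hospital. Every cluster contributes a baseline year plus control and intervention time, so level differences between types largely cancel. This stands for an analysis grouped by cluster, where the gain is 0–5%. It does not settle the matter, because the section names no working structure. An ordinary GEE takes one grouping level. Grouping by hospital with a single exchangeable correlation is a natural way to cover both sources, and the stated correlations of 0.36 and 0.39 give little reason to rule it out. Within a hospital, comparisons between clusters are largely comparisons between procedure types.

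Second, the Risk Index is operation-specific and may partly stand in for the level of risk by type. That also stands, and the simulations give it no credit. But the adjustment is planned in the Outcomes section and only considered in the Primary analyses section, so the protection is uncertain.

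Third, covariate detail belongs to the SAP, to which the protocol defers full details. Silence alone would be no finding. Here, though, the article does state the fixed effects and does name the adjusters. If the SAP already includes cluster type, the point is closed.

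**Conclusion.** The point holds as one of precision and robustness. Omitting cluster type leaves avoidable random error in the intervention estimate. The gain from including it ranges from nothing to a fall in SD from about 0.10 to 0.07–0.08, against a target effect of 0.288 on the log scale. It depends on the working correlation and on how far rates differ by type, and the latter is assumed here. Precision was not worse with type in any scenario examined.

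A reader might infer three stronger things, and the document supports none of them:

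- **That the estimate is biased.** Chance imbalance under randomization averages to about zero and is reflected in the robust standard error. In 250 null simulations per scenario, rejection rates were 0.060–0.084 without type terms and 0.044–0.072 with them (Monte Carlo SE about 0.015), which shows no clear inflation.
- **That secular trends differ by procedure type.** No section gives any trend by type. Even differing levels are implied rather than tabulated.
- **That the allocation should be rebalanced.** The Trial status section puts the end of recruitment at February 29, 2020 and says submission slipped from a plan to submit before that date. The sequence can be taken as run, so only the analysis can change.

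**What to change.** In the Primary analyses section, or in the SAP before database lock, add cluster type (cardiac, GI, joint, OB-GYN, spine, vascular) as a prespecified fixed covariate through five indicators, alongside step and phase. Add one sensitivity analysis with type-by-linear-time terms, labelled as such and not as the primary model. Leave the allocation as it is.

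The cost is five degrees of freedom with 105 clusters and one line of specification. Type of procedure is already a variable in the surgical database (Table 2), so no new data are needed.
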